# Ventilator-associated pneumonia prevention in the Intensive care unit using Postpyloric tube feeding in China (VIP study): study protocol for a randomized controlled trial

**DOI:** 10.1186/s13063-022-06407-5

**Published:** 2022-06-09

**Keywords:** Ventilator-associated pneumonia, Prevention, Postpyloric tube feeding, Randomized controlled trial, Efficacy, Safety

## Abstract

**Background:**

Ventilator-associated pneumonia is a challenge in critical care and is associated with high mortality and morbidity. Although some consensuses on preventing ventilator-associated pneumonia are reached, it is still somewhat controversial. Meta-analysis has shown that postpyloric tube feeding may reduce the incidences of ventilator-associated pneumonia, which still desires high-quality evidence. This trial aims to evaluate the efficacy and safety profiles of postpyloric tube feeding versus gastric tube feeding.

**Methods/design:**

In this multicenter, open-label, randomized controlled trial, we will recruit 924 subjects expected to receive mechanical ventilation for no less than 48 h. Subjects on mechanical ventilation will be randomized (1:1) to receive postpyloric or gastric tube feeding and routine preventive measures simultaneously. The primary outcome is the proportion of patients with at least one ventilator-associated pneumonia episode. Adverse events and serious adverse events will be observed closely.

**Discussion:**

The VIP study is a large-sample-sized, multicenter, open-label, randomized, parallel-group, controlled trial of postpyloric tube feeding in China and is well-designed based on previous studies. The results of this trial may help to provide evidence-based recommendations for the prevention of ventilator-associated pneumonia.

**Trial registration:**

Chictr.org.cn ChiCTR2100051593. Registered on 28 September 2021

**Supplementary Information:**

The online version contains supplementary material available at 10.1186/s13063-022-06407-5.

## Background

Ventilator-associated pneumonia (VAP) is defined as an infection of the pulmonary parenchyma in patients exposed to invasive mechanical ventilation for at least 48 h. It is one of the significant nosocomial infections in intensive care units (ICUs), contributing to increased ICU stay, morbidity, and mortality [1, 2]. Zhang et al. [1] recently reported the standardized VAP incidence and mortality of 33.7% and 34.5% in China. Many host- and treatment-related colonization factors, such as the severity of the patient’s underlying disease, prior surgery, exposure to antibiotics, and exposure to invasive respiratory devices and equipment, are essential in the pathogenesis of VAP [3–5]. Intravenous antimicrobial therapy is the cornerstone of VAP treatment, emphasizing prompt empiric treatment and early initiation of pathogen-specific treatment with appropriate duration [6–9]. However, despite the advances in the understanding and management of VAP over the past decade, the disease is associated with a significant economic burden and poor outcomes in ICU patients. In a systematic review, VAP conferred a twofold attributable risk of dying in the ICU, with an assignable cost ranging from USD$10,000 to $13,000 per patient [10]. Therefore, preventing VAP before it occurs is also a patient safety priority.

In addition to avoiding intubation and speeding extubation as the prevention strategies of VAP, a bundle of measures, which include elevation of the head of the bed, daily sedation vacations, assessment of readiness to extubate, deep-vein thrombosis prophylaxis, and daily oral care, are also considered standard of care [11]. However, VAP prevention strategies are variably applied in clinical practice [12–14], underscoring the need for reliable, safe, effective, and available VAP reduction strategies. As we know, enteral nutrition has been considered a modifiable risk factor for VAP development, mainly because of an increased risk of aspiration of gastric contents [15, 16]. The stomach may be one of the potential reservoirs of nosocomial pathogens that contribute to bacterial colonization via aspiration into the lower respiratory tract [3, 17–22]. Emerging as a clinically plausible strategy, postpyloric tube feeding (PTF) may represent a novel approach to preventing VAP through influencing microbiota, enhancing gut barrier function, and reducing gastric reflux and aspiration of gastric content [23–27]. Systematic reviews suggest that PTF reduces VAP by 53–55% compared with gastric tube feeding (GTF) [26, 28]. Nevertheless, most previous randomized trials are small-sample-sized, leading to a less persuasive conclusion. Meta-analyses of small and weak-powered trials often yield implausibly large treatment effects [25, 27]. Hence, the clinical benefits of PTF may be underestimated, and a large, well-powered multicenter trial is needed.

Despite widely accepted recommendations for PTF in nutrition delivery in ICU patients, few studies have assessed the ability of this intervention for VAP prevention. We, therefore, designed this prospective, multicenter, open-label, randomized control trial to validate the efficacy and safety of enteral nutrition via PTF inserted by endoscopy versus GTF in lowering VAP incidence, shortening mechanical ventilation days, ICU or hospital stay, and improving patient outcomes including mortality.

### Objectives

#### Primary objectives

The primary objectives of this trial are to:Determine the efficacy of PTF in lowering VAP incidence in critically ill patients receiving mechanical ventilation for more than 48 hDetermine the safety of PTF in lowering VAP incidence in critically ill patients receiving mechanical ventilation for more than 48 h

#### Secondary objectives

The secondary objectives of this trial are to:Determine the efficacy of PTF in improving mortality in critically ill patients receiving mechanical ventilation for more than 48 hDetermine the efficacy of PTF in shortening mechanical ventilation days, ICU or hospital stay, and if there is a benefit to decreasing the whole care cost in critically ill patients receiving mechanical ventilation for more than 48 hDetermine the efficacy of PTF in improving nutrition deficit and immune ability to infection in critically ill patients receiving mechanical ventilation for more than 48 h

## Methods/design

### Study design

The VIP study is designed as a prospective, multicenter, open-label, randomized, parallel-group, GTF-controlled (PTF vs. GTF 1:1) superiority trial in 4 tertiary care hospitals. The participating sites in this study include medical/surgical, medical, surgical, or emergency ICUs (see Table 1 for details of participating centers). Patient enrollment is expected to last for up to 36 months. The end of the study is defined as the last follow-up of the last enrolled patient. The trial has been registered at chictr.org.cn (ChiCTR2100051593). We used the Standard Protocol Items: Recommendations for International Trials (SPIRIT) reporting guidelines [29], and the SPIRIT checklist is attached in the Supplementary appendixes.

**Table 1 Tab1:** Research settings and names of each ethics committee

Research setting	Ethics committee name	Hospital rank and location
Maoming People’s Hospital	Medical Ethics Committee of Maoming People’s Hospital	Tertiary, Maoming, Guangdong, China
Guangdong Provincial People’s Hospital	Medical Ethics Committee of Guangdong Provincial People’s Hospital	Tertiary, Guangzhou, Guangdong, China
General Hospital of Southern Theater Command	Medical Ethics Committee of General Hospital of Southern Theater Command	Tertiary, Guangzhou, Guangdong, China
Heyuan People’s Hospital	Medical Ethics Committee of Heyuan People’s Hospital	Tertiary, Heyuan, Guangdong, China

### Patient and public involvement

Unlike patients living with long-term medical conditions such as diabetes and hypertension, most ICU patients unanticipated being admitted into ICU. They are relatively elder and lack clinical research education and experience, making it challenging to determine who will be the potential beneficiaries in attending our trial. However, we have planned to get our participants involved in the communication and education during the research process to increase awareness and knowledge, build confidence and control with self-management, and finally prevent and cure VAP.

### Recruitment

A well-trained study coordinator in each participating center that fulfills the requirement that a gastroscope can be performed at the bedside will be responsible for screening all potentially eligible patients based on the eligibility criteria. After confirming the patient’s eligibility for the trial, the study coordinator will obtain written informed consent from the patient or authorized representatives.

### Inclusion criteria

Patients are eligible for the trial if they are expected to receive mechanical ventilation for no less than 48 h, are over the age of 18 years, and require GTF [30]. Patients will be enrolled within 6 h of their endotracheal intubation.

### Exclusion criteria

Patients will be excluded if they are intubated for more than 6 h, have contradictions for feeding tube placement, or present conditions which will preclude the diagnosis, monitoring, and assessment of VAP development. Detailed exclusion criteria are summarized in Supplementary Appendix 1.

### Drop-out criteria

Patients who meet eligibility criteria and write an informed consent form (see Supplementary Appendix) to participate but fail to accomplish the study process are regarded as drop-out cases if they meet any of the following criteria: (1) the participant or the legal representative requests withdrawal at any time, (2) the investigator considers it inappropriate to continue for safety purpose, and (3) additional reasons for the participant to discontinue from an investigator’s medical perspectives. The drop-out rate must be no more than 10% in this trial.

### Diagnosis of ventilator-associated pneumonia and adjudication process

VAP should rather be suspected in patients with clinical signs of infection, such as at least two of the following criteria: new onset of fever, purulent endotracheal secretions, leukocytosis or leucopenia, increase in minute ventilation, a decline in oxygenation, or increased need for vasopressors to maintain blood pressure [31].

In cases of suspected VAP, the Clinical Pulmonary Infection Score (CPIS) and Sequential Organ Failure Assessment (SOFA) score are assessed. Bedside anteroposterior chest radiography, arterial blood gas analysis, blood cultures, and quantitative sampling of the lower respiratory tract (by either bronchoalveolar lavage or endotracheal aspiration, at the discretion of the attending physician) [32] are performed before any antibiotics are administered.

An adjudication committee composed of one senior radiologist and two senior intensivists unaware of the trial-group assignments reviewed all patients’ medical charts and adjudicated all respiratory tract infections. The intensivists have access to all monitored data, chest radiographs obtained during the ICU stay, and microbiologic documentation. Two of them analyzed data from every patient independently, and in case of disagreement, the third one arbitrated the diagnosis of VAP. Such infections are defined as early if they occurred within 7 days after randomization and as late if they occurred after 7 days, according to an adjudication chart (Supplementary Appendix 2) and the definition of VAP. All secondary infections that happened during the ICU stay are also recorded.

A diagnosis process to confirm reported clinical VAP is defined in a standardized approach with the use of criteria from the 2020 Food and Drug Administration guidance for diagnosis and confirmation of VAP, which relies on clinical, laboratory, and radiologic criteria (patients have to meet all three types of standards). The flow chart for diagnosis and confirmation of VAP is summarized in Supplementary Appendix 3.

### Endotracheal tube, feeding tube, and enteral nutrients

According to Good Manufacturing Practice guidelines, all feeding tubes are prepared by Henan Anesthesia Medical Technology Co, Ltd. All endotracheal lines and enteral nutrients are provided by participating centers according to their routine practices. All studying materials aforementioned are shipped to each participating center by express service for a 14-day supply and stored in a cool, well-ventilated place to avoid direct sunlight.

### Assignment of interventions

#### Sequence generation for allocation

Following informed consent and confirmation of inclusion and exclusion criteria, participants on mechanical ventilation will be randomly assigned in a 1:1 ratio to receiving either PTF or GTF. Allocation sequences are generated by computer-generated random numbers using the R package *blockrand* [33]. Stratified block randomization is employed to avoid inter-group differences (study or control group) due to differences in the source of patients in different hospitals. Each participating center is served as a stratification factor, and then the subjects in each ICU are randomized into other blocks. The subjects will be consecutively assigned when entering the trial. To reduce the predictability of a random sequence, blocking details are provided in a separate document that is unavailable to those who enroll participants or assign interventions.

#### Allocation concealment mechanism

A central randomization system is set up to conceal the allocation to investigators. To prevent early knowledge of treatment assignment and disruption of the assignment sequence, investigators must complete the clinical trial entry form attached to the case report form (CRF) and obtain the informed consent form before disclosing the unique sequence number and assignment group. Randomization methods and block sizes are blinded until all data analyses are completed.

#### Allocation implementation

Each center’s investigator and authorized clinicians will enroll subjects according to the protocol’s eligibility criteria and allocate the newly registered patient into the corresponding group according to the unique number for specific assignments acquired from a randomization squad. The squad fetches the assignment number through a prepared online central randomization system, which will be sent to the investigator via instant messaging software like WeChat once the informed consent form is signed.

### Interventions

Patients who meet the enrollment criteria will be randomized 1:1 to either the PTF or the GTF group, receiving postpyloric or gastric tube feeding, respectively, with other treatments exactly the same.

#### Endoscopic feeding tube placement

A nasogastric feeding tube is inserted by nursing staff for the control group. Currently, in our clinical practice, the postpyloric feeding tube can be established by self-propelled dynamics from the gut with the assistance of prokinetic agents [34–36] and using a rescued bedside tube placement method by ICU physicians when necessary [37]. However, despite the short learning curve [38] and easy availability of the methods mentioned above, especially in the advantage of some decision support tools [39, 40], we otherwise decided to employ the endoscopic approach to establish the postpyloric feeding tube promptly and reliably for the study group. Hence, experienced endoscopists must be equipped when participating centers are recruited. In most ICUs currently in China, no special endoscopists are regularly prepared. In this case, a training course on endoscopic postpyloric tube placement is established to equip the physicians to become experienced endoscopists in the ICU.

Detailed training protocol is attached as Supplementary Appendix 4 in this manuscript. The essential procedures of endoscopic tube placement are as follows:

Patients are provided with oxygen inhalation, and ECG and blood oxygen saturation are monitored. After the patient is narcotized, they take the left lying position. During the operation, no secretion could be left in the mouth. A lubricated nasointestinal tube, approximately 25cm deep, is inserted through the nostrils and sent to the gastric lumen by gastroscopy. The esophagus, stomach, and duodenum are observed to confirm the absence of lesions or obstruction. The head end of the nasointestinal tube is clamped with foreign body forceps, and it is slowly pushed into the descending part of the duodenum to fix the nasointestinal tube. The gastroscope is returned to the gastric cavity, and the foreign body forceps are released into the gastric cavity. After about three times, they are transported to about 20–40 cm below the Treitz ligament. After the nasointestinal tube is fixed, the gastroscope and the nasointestinal tube guidewire are withdrawn.

#### Nutrition support protocol

In both groups, energy goals are set at 25 kcal per kg of ideal body weight per day, and the protein target is 1.2–2.0 g per kg of ideal body weight per day. Glucose control targets are set following international guidelines [41–43]. Incidences in which the patient develops an intolerance to EN (diagnosed when vomiting, diarrhea, abdominal pain, or abdominal distension occurred) are recorded. In these cases, the rate of feeding and EN are gradually reduced as tolerated. If the nutrition goal is not reached within 7 days, parenteral nutrition is provided.

#### Concomitant interventions

Routine use of a bundle of measures for the prevention of VAP (elevation of the head of the bed, daily sedation vacations and assessment of readiness to extubate, and deep-vein thrombosis prophylaxis) and daily oral care are highly recommended, and specific attention is given to standardize patient care [11].

Participants may receive management preventing from VAP following the 2016 Clinical Practice Guidelines for the Management of Adults with Hospital-acquired and Ventilator-associated Pneumonia by the Infectious Diseases Society of America and the American Thoracic Society, mainly including (1) manage patients without sedation whenever possible; (2) interrupt sedation daily; (3) assess readiness to extubate daily; (4) perform spontaneous breathing trials with sedatives turned off; (5) facilitate early mobility; (6) utilize endotracheal tubes with subglottic secretion drainage ports for patients expected to require more than 48 or 72 h of mechanical ventilation; (7) change the ventilator circuit only if visibly soiled or malfunctioning; and (8) elevate the head of the bed to 30–45. If any, the use of all the above maneuvers should be documented in the electronic case report form (eCRF).

### Outcome measurements

Participants will be evaluated clinically and through laboratory testing according to Table 2. The following data will be recorded: demographics, VAP diagnosis, concurrent medical conditions and comorbidities, inclusion and exclusion criteria, the severity of illness and organ dysfunction scores, vital signs and laboratory results, potential confounding co-interventions (life-sustaining therapies and use of sedatives or vasopressors), and outcomes (vital status at ICU and hospital discharge, day 28 and day 90, ICU and hospital length of stay).

**Table 2 Tab2:** Trial schedule of the VIP study

Timepoint	Baseline	^**a**^Interventions									Termination
	^b^D0	D1	D2, ^c^N1	D..., N...	D4	D5	D6	D7	D8, N7	D…	D28
Eligibility screening	**×**										
Informed consent obtaining	**×**										
Randomization	**×**										
Medical history collection	**×**										
Population data collection	**×**										
Baseline data collection	**×**										
Evaluation of major adverse tube-associated events (MATE)		**×**	**×**								
Evaluation of ^d^EN related adverse events			**×**	**×**	**×**	**×**	**×**	**×**	**×**	**×**	**×**
Evaluation of serious adverse events		**×**	**×**	**×**	**×**	**×**	**×**	**×**	**×**	**×**	**×**
VAP episode		**×**	**×**	**×**	**×**	**×**	**×**	**×**	**×**	**×**	**×**
Microorganisms causing VAP		**×**	**×**	**×**	**×**	**×**	**×**	**×**	**×**	**×**	**×**
Duration of mechanical ventilation		**×**	**×**	**×**	**×**	**×**	**×**	**×**	**×**	**×**	**×**
SOFA score		**×**	**×**	**×**	**×**	**×**	**×**	**×**	**×**	**×**	**×**
CPIS score		**×**	**×**	**×**	**×**	**×**	**×**	**×**	**×**	**×**	**×**
Serum albumin and C-reactive protein		**×**	**×**						**×**		
ICU-acquired infections (bloodstream, urinary tract, catheter-related, and other infections)		**×**	**×**	**×**	**×**	**×**	**×**	**×**	**×**	**×**	**×**
Day calorie target		**×**	**×**	**×**	**×**	**×**	**×**	**×**	**×**	**×**	
Day actual calorie		**×**	**×**	**×**	**×**	**×**	**×**	**×**	**×**	**×**	
Day calorie deficit		**×**	**×**	**×**	**×**	**×**	**×**	**×**			
Ventilator free		**×**	**×**	**×**	**×**	**×**	**×**	**×**	**×**	**×**	**×**
Transfer out of ICU		**×**	**×**	**×**	**×**	**×**	**×**	**×**	**×**	**×**	**×**
ICU survival		**×**	**×**	**×**	**×**	**×**	**×**	**×**	**×**	**×**	**×**
Discharge		**×**	**×**	**×**	**×**	**×**	**×**	**×**	**×**	**×**	**×**
Hospital survival		**×**	**×**	**×**	**×**	**×**	**×**	**×**	**×**	**×**	**×**
28-day survival											**×**

Eligibility screening includes diagnosis, inclusion/exclusion criteria, urine pregnancy test for female, demographics, medical history, and physical examination

*CPIS* Clinical Pulmonary Infection Score, *EN* Eenteral nutrition, *MATE* Major adverse tube-associated event, *SOFA* Sequential Organ Failure Assessment score

^a^Intervention means postpyloric tube feeding

^b^D means day from enrollment

^c^N means day from enteral nutrion

^d^EN-related adverse events include abdominal distension, gastric retention, vomiting, diarrhea, and aspiration of gastric contents

#### Primary efficacy endpoint

The primary efficacy endpoint of this study is the proportion of patients with at least 1 VAP episode.

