### Data management

Trained staff will perform data management at each center using the Electronic Data Capture (EDC) system (https://www.mmphcrc.com/pdf/medicalHistory/vapcrf.html). The EDC system’s reliability, access control, and traceability will guarantee the quality of trial data management. Data collection will be restricted to those variables necessary to define baseline patient characteristics (demographics, VAP diagnosis, concurrent medical conditions and comorbidities, inclusion and exclusion criteria, severity of illness and organ dysfunction scores, vital signs, and laboratory results), the delivery of the nutrients, potential confounding co-interventions (life-sustaining therapies, and use of vasopressors or sedatives), and outcomes (vital signs at ICU and hospital discharge, day 28, length of stay in ICU and hospital). Randomized participants will be followed until either death or 28 days after randomization, whichever comes first. Study staff will attend follow-up by either direct contact with the patient or the next of kin. Participants who withdraw from the study will be followed up according to the follow-up schedule and analyzed on the ITT principle.

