#### Analyses set

The study protocol mention that analysis will be done considering the “intention to treat” principle. However, some randomized patients did not allow feeding tube insertion (gastric or postpyloric) during study conduction due to illness severity, or the attending physician decided not to insert the tubes. Those cases are not excluded from the analyses. Patients who complete the randomization, regardless of whether they completed the trial or received the treatment in the designated group, are retained in the original group for analysis. The randomization information is maintained to the maximum extent.

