#### Intention-to-treat set (ITTS)

ITTS refers to the ideal population of subjects meeting the ITT principles. To best retain the randomized information, ensure that the differences in trial results are attributed to the differences in treatment, and make the effect of treatment (postpyloric feeding) best assessed, the principle of ITT analysis is adopted. ITT set (ITTS) included all randomized patients, regardless of whether they have received nasogastric tube placement, completed the trial, or received the treatment of this group, all of whom remain in the original group for analysis.

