#### Data analysis

All analyses will be performed according to the ITT principle. A *P* value < 0.05 is considered statistically significant. All tests are two-sided with no adjustment for multiple comparisons. Continuous variables are reported as means and standard deviations or medians and interquartile ranges. Categorical variables are reported as proportions. Pearson’s chi-squared test and adjusted multivariable analysis will be applied for the primary outcome. We plan to perform subgroup analyses for the primary outcome for predefined variables: the proportion of patients with at least 1 VAP episode. All the other data, including age, gender, body mass index (weight, height), SOFA score, primary admission diagnosis, coexisting illness, and type of admission, will be presented as descriptive results. Pearson’s chi-squared test will compare incidence or mortality outcomes between groups. The *t*-test will compare total VAP episodes, SOFA scores, time to VAP onset from mechanical ventilation, mechanical ventilation duration, ICU and hospital lengths of stay, inflammatory biomarkers, and function indicators between groups. A paired *t*-test or repeated measures ANOVA will be used to compare baseline and changes during the intervention.

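### The primary endpoint counts death before VAP as no VAP, so a difference in early deaths would shift the VAP comparison by a few points, and no stated analysis links the two

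*Protocol article*

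**What the plan says.** Four statements in the protocol article together fix what the primary comparison measures.

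- **Endpoint** (Primary efficacy endpoint): "The primary efficacy endpoint of this study is the proportion of patients with at least 1 VAP episode". It has no clause for death.
- **Population** (Intention-to-treat set and Analyses set): "ITT set (ITTS) included all randomized patients". Patients who complete randomisation, "regardless of whether they completed the trial or received the treatment in the designated group, are retained in the original group for analysis".
- **Follow-up** (Data management): "Randomized participants will be followed until either death or 28 days after randomization, whichever comes first". VAP can no longer be observed once a patient has died.
- **Test** (Data analysis): Pearson's "chi-squared test and adjusted multivariable analysis will be applied for the primary outcome", two-sided, where a P "value < 0.05 is considered statistically significant".

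Death appears elsewhere only. ICU, hospital and day-28 mortality and ventilator-free days are separate secondary endpoints. Cumulative VAP incidence and time to VAP onset are also secondary. Under Data analysis, incidence and mortality outcomes are compared by chi-squared test and time to VAP onset by t-test.

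**The concern.** Death before VAP is a competing event: it removes the patient from risk of the outcome. The stated combination of endpoint, population and test scores that death as no VAP, exactly like an extubation without pneumonia. If early death differs between the arms, the VAP proportions differ even where feeding route has no effect on VAP.

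The article gives reasons to allow for a difference in either direction. A secondary objective is that postpyloric feeding improves mortality. The arms also differ by a procedure soon after intubation: controls have a nurse-placed tube, while postpyloric patients have a gastroscopy ("After the patient is narcotized, they take the left lying position"). The listed safety endpoints for tube placement include desaturation, bleeding and perforation. Deaths are not rare in this setting: the Background cites "standardized VAP incidence and mortality of 33.7% and 34.5% in China".

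At stake is how a moderate VAP difference is read. The primary P value cannot separate fewer pneumonias from fewer patients living long enough to develop one.

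**Working it through.** **Inputs from the article.** 924 patients at 1:1, so 462 per arm; control VAP proportion 33.7%; relative reduction 51.4%; two-sided 0.05. The planned effect reproduces: 0.337 × 0.514 = 0.173, which leaves 0.337 − 0.173 = 0.164 in the postpyloric arm.

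**Assumptions, not in the article.** In the gastric arm 10% die before VAP. In the postpyloric arm the proportion d is 5%, 15% or 20%. Patients who do not die early have the same VAP risk q in both arms, so there is no true effect on VAP.

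**Step 1: the shift in VAP.** q = 0.337 / (1 − 0.10) = 0.374. The postpyloric VAP proportion is (1 − d) × q. VAP or death is that figure plus d; in the gastric arm it is 0.337 + 0.10 = 0.437.

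| Pre-VAP death, postpyloric | VAP, postpyloric | Shift from 33.7% | VAP or death (gastric 43.7%) |
|---|---|---|---|
| 5% | 0.95 × 0.374 = 35.6% | +1.9 points | 40.6% |
| 15% | 0.85 × 0.374 = 31.8% | −1.9 points | 46.8% |
| 20% | 0.80 × 0.374 = 30.0% | −3.7 points | 50.0% |

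In each row VAP alone and VAP or death move in opposite directions. The 5% row assumes that patients spared an early death stay ventilated and share the average VAP risk.

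**Step 2: the chance of a significant result in the direction of the shift.** With s0 = √[2p̄(1 − p̄)/462] and s1 = √{[p1(1 − p1) + p2(1 − p2)]/462}, the chance is Φ[(|Δ| − 1.96·s0)/s1].

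- d = 20%: (0.0374 − 0.0601)/0.0306 = −0.74, giving 23%, favouring postpyloric feeding.
- d = 15%: (0.0187 − 0.0605)/0.0309 = −1.35, giving about 9%, favouring postpyloric feeding.
- d = 5%: (0.0187 − 0.0614)/0.0313 = −1.36, giving about 9%, against postpyloric feeding.

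With no difference in early death the figure is 2.5% in each direction.

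**Step 3: the limit of the effect.** Significance at 462 per arm needs an observed difference of about 6 points. For the artefact alone to reach that, d must be about 26%: 0.74 × 0.374 = 27.7%, or 6.0 points below 33.7%. To mimic the planned 16.4%, d would have to be 1 − 0.164/0.374 = 56%, against 10% in controls.

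**Step 4: a second model.** Constant hazards over 28 days were used, with 33.7% VAP, 40% extubated without VAP and 10% to 25% dying before VAP in the control arm (the last two assumed), and the same VAP hazard in both arms. A postpyloric death hazard 1.5 times the control's lowers VAP by 1.3 to 3.6 points; 2 times, by 2.5 to 6.6 points; half the control's raises it by 1.3 to 4.5 points. The directions agree with Step 1, and the top of the range needs both a doubled hazard and 25% control deaths before VAP.

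**Step 5: would the mortality endpoint show it?** Assume also that 34.5% of VAP patients die in both arms. At d = 20%, mortality is 0.20 + 0.345 × 0.300 = 30.3% against 0.10 + 0.345 × 0.337 = 21.6%, significant in about 86% of trials. At d = 15% it is 0.15 + 0.345 × 0.318 = 26.0% against 21.6%, significant in about 34%.

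**The case against.** The strongest reply is that this is ordinary analysis-plan content. Only a journal article is at hand, it never says in words how death is scored, and an unseen plan could set a rule. That stands in part: the absence of further supportive analyses is not itself an error. But the article does fix the endpoint, population, follow-up and test, and the scoring of death follows from them. It also fixes a t-test for time to VAP onset. Patients without VAP have no onset time, so that test compares only those who developed it and cannot account for those who died first.

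Second, mortality is prespecified in the same population, serious adverse events are reported within 24 hours, and there is a data monitoring committee. This stands for a large imbalance, as Step 5 shows. It is weaker for a 5-point excess, although the VAP distortion there is only 1.9 points.

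Third, with complete 28-day follow-up the primary proportion already is the day-28 cumulative incidence of VAP with death competing. This is correct, so asking for that curve's day-28 value would add little. The cause-specific hazard ratio and the composite are what add information.

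Fourth, nothing in the article shows that bedside endoscopy changes mortality. That also stands; the death rates above are scenarios.

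A reader might go further and infer that excess deaths would pass for VAP prevention and that lives saved would show as more VAP. The documents do not support that as a general statement. The first needs an imbalance far larger than assumed here to match the planned effect, and the second holds only if survivors remain ventilated and at risk.

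**Conclusion.** The point holds in a limited form. As specified, the primary comparison treats death before VAP as freedom from VAP, and no stated analysis connects the VAP result to deaths. Under assumed pre-VAP death of 10% against 5% to 20%, the distortion is about 2 to 4 points. That is roughly one to two thirds of the 6 points needed for significance and well short of the planned 17.3. It could therefore colour a moderate result but could not manufacture the designed one. The size rests on pre-VAP death rates that the article does not give and on equal VAP risk among patients who do not die early. The direction in which better survival raises VAP depends on survivors staying at risk. The article's mortality endpoints would usually reveal a large imbalance, but they would not say how to read the VAP result beside it. This is a worthwhile improvement to the plan and does not invalidate the endpoint.

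**What to change.** Keep the primary endpoint and its test. Before outcome data by arm are seen, prespecify two supportive analyses:

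1. VAP or death by day 28 in all randomised patients, by the same chi-squared test.
2. In place of the t-test of time to VAP onset, a cause-specific hazard ratio for first VAP, with death and extubation as competing events.

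Report both, with mortality, beside the primary result. Neither should be a condition for claiming success: requiring the composite to agree would create a new success criterion and could block a true VAP reduction by chance.

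The cost is wording only. The trial schedule already records VAP episodes, ventilation duration, ventilator-free status and survival to day 28, so no visits or patients are added. The downside is that the composite is diluted by deaths unrelated to feeding and is less sensitive to a real VAP effect than VAP alone, which is why it belongs in a supporting role.
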